# Comparing the effects of individualized, standard, sham and no acupuncture in the treatment of knee osteoarthritis: a multicenter randomized controlled trial

**DOI:** 10.1186/1745-6215-14-129

**Published:** 2013-05-07

**Keywords:** Acupuncture, Syndrome differentiation, Sa-am acupuncture, Individualized treatment, Knee osteoarthritis, RCT

## Abstract

**Background:**

Acupuncture is an effective yet complex therapy, integrating syndrome differentiation, selection of appropriate acupoints and skillful needling techniques. Clinicians carefully tailor acupuncture treatment to each patient. However, most clinical trials of acupuncture have been based on a standardized formula of points for every patient without properly accounting for individualdifferences and, as a result, have not been reflective of the true efficacy of clinical practice. To determine the efficacy of meridian-based syndrome differentiation and Sa-am acupuncture, we have designed a simple pragmatic trial providing individualized treatments while working within a general framework.

**Methods/Design:**

The study is designed to be a parallel, patient- and assessor-blind, randomized controlled trial (RCT). A total of250 patients with knee osteoarthritis (OA) will be recruited from two independent hospitals, Semyung University Oriental Medicine Hospital in Chung-ju and Dongguk University Oriental Hospital in Ilsan, South Korea. Patients will be randomly allocated into four treatment groups: 1. individualized, meridian-based syndrome differentiation and Sa-am acupuncture treatment;2. standard acupuncture treatment;3. sham acupuncture treatment; and 4. no acupuncture treatment. Patients in groups 1 to 3 will be treated by certified oriental medicine doctors twice a week for 6 weeks. The primary outcome measure will be the self-reported total Western Ontario and McMaster Universities Osteoarthritis Index (WOMAC) score change. The trial will also include secondary outcome measures.

**Discussion:**

This trial is designed to determine the efficacy of individualized acupuncture treatment in patients with knee OA by comparing the differences between individualized, standard, sham and no acupuncture treatments. The results of this trial may validate the efficacy of individualized acupuncture therapy, encouraging its widespread use.

**Trial registration:**

ClinicalTrials.gov: NCT01569230

## Background

Most clinical trials are designed to evaluate the efficacy and safety of medical treatment [1]. Recently, there has been increased interest in using acupuncture methods and other alternative medicines for treating diseases [2], especially those without effective conventional treatment options, such as osteoarthritis(OA) [3]. OA is one of the top ten disabilities affecting people in developed countries and significantly impacts the lives of many people [4]. At present, however, no medications are available to effectivelytreat OA. Since many patients are turning to alternative therapies [5-7], it has become necessary to determine their efficacy. For example, many clinical trials have been performed to evaluate the efficacy of acupuncture [8]. However, the results from these studieshave been criticized owing to a lack of definitive evidence regarding the efficacy of acupuncture; some studies suggest that acupuncture has clear benefits, whereas others are less conclusive [8].Many practicing oriental medicine doctors believe that this lack of definitive evidence is due to the absence of individualized syndrome differentiation from the trial design, a fundamental aspect of traditional Chinese medicine [9].

Many clinical trials on acupuncture have been explanatory in nature, emphasizing the standardization of treatments, rather than taking a pragmatic approach and compiling clinically relevant data [10]. Clinical research can be divided into two main categories, explanatory and pragmatic. Explanatory trials focus on evaluating the efficacy of a treatment in ideal, standardized environments, whereas pragmatic trials seek to determine the efficacy in clinically applicable settings [11,12]. Acupuncture therapy involves various elements unique to individual patients. For example, it must consider the signs and symptoms of each patient in differential symptom diagnosis, select the proper acupoints for a particular illness and utilize a refined needling technique [13]. In addition, to enhance the efficacy of treatment, the acupoints selected must be determined based on an understanding of each patient's individual characteristics. Hence, explanatory trials based on a single set of standardized acupoints are not appropriate for testing the efficacy of acupuncture [10].

Although pragmatic trials more closely mimic clinical settings, they also have inherent flaws. For exampletreatments often include minute variations, depending on each clinician's diagnostic methods and needling techniques, making the trials difficult to replicate [14-16]. Thus, it is necessary to enhance the reproducibility of pragmatic trials testing individualized acupuncture therapy, so that other practitioners may be better able to replicate the general techniques, while still mimicking routine clinical practice [12].

In this study, we propose to treat patients diagnosed with knee OA with anindividualized, meridian-based [17]syndrome differentiation acupuncture method. For each patient, we will select the most appropriate of the many methods available, including the Eight Principles, the Zang-fu organ system, the Qi-Blood-Yi method and the Triple Burner [18].Meridian-based syndrome differentiation was chosen because it allows the selection of specific acupoints connected to the area of pain [19-21] and considers the particular characteristics of each patient, while still being a generalized, reproducible method. Furthermore, a recent survey of oriental medicine practitioners in Korea reported that meridian-based syndrome differentiation, in conjunction with Sa-am acupuncture, is the most commonly used form of acupuncture treatment in Korean clinical practice [21].

This trial is therefore designed to assess the efficacy of meridian-based syndrome differentiation acupuncture therapy. Patients will be randomly allocated into four treatment groups: 1. individualized, meridian-based syndrome differentiation and Sa-am acupuncture treatment;2. standard acupuncture treatment;3. sham acupuncture treatment; and 4. no acupuncture treatment.

## Methods/Design

### Study design

This prospective parallel, single-blinded (assessor and patient), randomized controlled trial (RCT) is designed to assess the efficacy and safety of individualized acupuncture therapy in patients with knee OA. It will be conducted at two clinical research centers in South Korea, Semyung University Oriental Medicine Hospital in Chung-ju and Dongguk University Oriental Hospital in Ilsan, with patients divided into four parallel groups. The research protocol has been approved by the institutional review board (IRB) at each center, and each patient will be asked to provide informed consent.

### Recruitment

Participants will be recruited through advertisements in local newspapers and bulletin boards in each trial center, with a target sample size of 250 patients. All patients will be screened initially by telephone with regard to selection criteria. If appropriate, their eligibility will be determined by both an orthopedist and a radiologist through physical and radiological examinations.

### Participants

Patients will be selected from outpatients aged 40 years to 80 years with painful knee OA, as defined by the American College of Rheumatology (ACR) [22]. Patients with pain in one or both knees during the previous 3 months or longer and rated >40 mm on a visual analog scale (VAS; 0 to 100 mm) will be selected for the trial.Patients will be excluded from the study if they have: 1. trauma or surgery on the knee(s) within 6 months prior to enrollment, causing pain or functional problems; 2. a history of prolotherapy, with injections of hyaluronic acid or cortisone within the previous 3 months; 3. physical or laboratory findings indicating infection, the presence of an autoimmune disease or inflammatory arthritis; 4. serious organic disease (for example arrhythmia, angina pectoris, stroke, asthma) with resultant severe dysfunction; 5.more severe pain in regions other than the knee joint; or 6.if they are pregnant. In addition, to ensure that the results from this study are only due to the treatments from this study, all participants will be required to not have received acupuncture therapy for 2 weeks prior to entering this trial.

### Randomization and blinding

Patients will be randomized by an independent statistician using a computerized, random-number generator through the block-randomization method of SAS version 9.1(SAS Institute Inc, Cary, NC, USA) for sequence generation. Separate randomization files will be created for each of the two sites. Allocations will be concealed using sealed, opaque envelopes. After the assessor has screened the patient for inclusion and the patient has signed the informed consent form, the next envelope in the sequence will be provided, immediately prior to treatment, to the certified oriental medicine doctor who will perform acupuncture. By this method, a total of 250 participants will be randomly assigned to the four groups. Although all patients and their screening assessors will be blinded to treatment, the certified oriental medicine doctor applying acupuncture will not.

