#### General acupuncture preparation and needling technique

To ensure that the study is single-blinded and that patients are not aware of the differences between treatments, we propose using a Park sham needle guide-tube [23,24] for all three acupuncture treatment groups. This will ensure that the patient will not observe any outwardly discernible differences among individualized, standard and sham acupuncture, although the penetration of the needles will differ among these three groups.

Prior to needle insertion, the area of the skin will be sterilized. Acupuncture will be performed using sterile stainless steel disposable acupuncture needles (DongBang Acupuncture Inc, Korea).The depth of insertion at each point was predetermined to be within the normal range of 8 mm to 30 mm, depending on the location of the point. Following needle insertion, the acupuncture point will be stimulated using bidirectional rotations of the needle sleeve, to achieve the sensation known as Deqi.

In patients randomized tothe individualized and standard acupuncture groups, an electroacupuncture device (STN-111,StraTek Co, Korea) will be used to provide electrical stimulation to the proximal acupoints, with the clinician adjusting the intensity so that the patientfeels an uncomfortable but not painful sensation. The needles will be kept in place for 20 minutes.

Due to ethical considerations, patients who have previously taken analgesics and non-steroidalanti-inflammatory drugs (NSAIDs) will be allowed to continue to take these medications during the study period. However, we will request that patients avoid physical therapy as much as possible to ensure that our results reflect the role of acupuncture therapy, not other forms of treatment. Patients will be questioned about having received medication at each visit and this information will be recorded for analysis of the data.

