#### No acupuncture treatment group

Patients in the control group will receive no acupuncture treatments, but will be assessed at each visit.

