## Discussion

The individualized acupuncture treatment method proposed in this study, consisting of meridian-based syndrome differentiation and Sa-am acupuncture, is not only the most commonly method used by certified oriental medicine doctors in Korea to treat patients with OA [21,25], but can be generalized for widespread use in the future. In this trial, we will evaluate the efficacy of this individualized treatment method by comparing it with standard, sham and non-treatment groups.

The acupuncture methods employed in this study are the closest to actual clinical practice and can be used in future studies. Moreover, the techniques of meridian based and Sa-am acupuncture that we will use in this study are based on the consensus of many certified oriental medicine doctors in Korea. In addition, we will strive to conduct a high quality, single-blinded clinical trial by ensuring that the assessors and participants are not informed of the type of treatment, by using a variety of controls including Park sham acupuncture, and providing trial-specific training of the exact methods used to well-qualified and certified oriental medicine doctors.

In conclusion, this research involves three different controls, and it will help elucidate the efficacy of individualized acupuncture versus standard, sham and no acupuncture groups.

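### Patient blinding is claimed for the whole four-arm trial, but the no-acupuncture arm is open, so that contrast on a self-reported primary outcome cannot isolate a needling effect

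*Protocol article*

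**What the plan says.** The blinding claim is made for the trial as a whole in three places, with an echo in a fourth.

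- Abstract, Methods/Design: "The study is designed to be a parallel, patient- and assessor-blind, randomized controlled trial (RCT").
- Study design: "This prospective parallel, single-blinded (assessor and patient), randomized controlled trial (RCT"), in a section that goes on to describe four parallel groups.
- Randomization and blinding, directly after the sentence assigning 250 participants to four groups: "Although all patients and their screening assessors will be blinded to treatment, the certified oriental medicine doctor applying acupuncture will not".
- Discussion: quality is to be secured by "ensuring that the assessors and participants are not informed of the type of treatment".

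The fourth arm is described in one sentence: "Patients in the control group will receive no acupuncture treatments, but will be assessed at each visit".

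The primary endpoint is patient-rated: "The primary outcome measure will be the self-reported total Western Ontario and McMaster Universities Osteoarthritis Index (WOMAC) score change". The Discussion says that the efficacy of the individualized method will be evaluated against the standard, sham and untreated groups, and the Statistical analysis plan section compares all four groups in one ANCOVA.

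**The concern.** Patients in group 4 know that they are untreated, and patients in groups 1 to 3 know that they are not in group 4. Any contrast with group 4 is therefore unblinded on both sides, and the unblinded person is the one who scores the primary endpoint. Among the secondary endpoints, the WOMAC pain subscale, walking VAS and patient global assessment are also patient-rated, and treatment success is derived from WOMAC.

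What is at stake is interpretation. A difference between individualized and no acupuncture combines whatever needling does with hope in the treated arm, disappointment in the untreated arm, the attention that comes with treatment sessions, and a tendency to report accordingly. The article calls the trial patient-blind without exception and names the untreated group among the comparisons for efficacy. Nowhere does it say that this contrast is open or limit what it may show.

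**Working it through.** **1. Which arms can be patient-blind?** The stated measures, set against the arms:

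| Measure | Section | Groups 1 to 3 | Group 4 |
|---|---|---|---|
| Park guide-tube | General acupuncture preparation and needling technique: "we propose using a Park sham needle guide-tube [23,24] for all three acupuncture treatment groups" | yes | no |
| Non-penetrating device and mock stimulator | Sham acupuncture | yes (used in group 3 to mimic groups 1 and 2) | no |
| Cloth barrier at the neck | Quality assurance; it hides the needling from view | yes | nothing to hide |

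The article's own statement of what is indistinguishable stops at three arms: "the patient will not observe any outwardly discernible differences among individualized, standard and sham acupuncture". Together with the description of group 4, this contradicts the claim that every patient is blinded.

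**2. How much of the trial is involved?** Allocation is 2:2:1:1, so group 4 is 1/6 of patients: 33 of 198 evaluable, or 250/6 ≈ 42 of those randomized. It enters one of the three contrasts of individualized acupuncture with a comparator.

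**3. The plan's own figure.** Inputs from Sample size: difference 2.34, SD 3.35, two-sided 0.05, power 80%.

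- n per arm = 2 × (1.960 + 0.842)² × 3.35² / 2.34² = 32.17, rounded up to 33.
- With 33 in each smaller arm at 2:2:1:1, N = 6 × 33 = 198, as stated.
- 198 / (1 − 0.20) = 247.5, so 248, close to the 250 stated.

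The planned size is reproduced, and nothing in this point changes it.

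**4. Illustration of what open self-rating could do.** The article gives no bias size. The shift below is an assumption, shown as a range.

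- Standard error for 66 versus 33: 3.35 × √(1/66 + 1/33) = 0.714.
- An assumed shift of d SD equals d × 3.35 points and gives noncentrality d / √(1/66 + 1/33).
- Probability of a significant two-sample t-test (two-sided 0.05, 97 df, noncentral t) when needling has no specific effect:

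| Assumed shift | Points | Share of 2.34 | Noncentrality | P(significant) |
|---|---|---|---|---|
| 0 | 0 | 0% | 0 | 5% |
| 0.1 SD | 0.335 | 14% | 0.47 | 7.5% |
| 0.2 SD | 0.67 | 29% | 0.94 | 15.3% |
| 0.4 SD | 1.34 | 57% | 1.88 | 45.9% |

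This is an unadjusted comparison. The planned ANCOVA adjusts for baseline WOMAC, so its exact figures would differ.

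**The case against.** **An untreated arm cannot be blinded, and a reader can see that.** The needling-technique section already restricts the guide-tube and the indistinguishability statement to the three acupuncture groups, and the fourth arm is described openly. A no-treatment arm beside a sham arm is a legitimate choice in a trial that calls itself pragmatic. All of this stands: nothing is hidden and the design need not change. But the sentence on blinding says all patients, and the two design labels carry no exception. The Discussion sentence is weaker evidence, because it is linked there to the use of sham controls.

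**A reader might infer that the untreated contrast cannot show efficacy at all.** That goes too far. An open contrast can estimate the overall effect of offering acupuncture. What it cannot do is attribute that effect to needling.

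**A reader might infer that sham and no acupuncture are treated as equivalent controls, or that a positive result would be reported as blinded evidence.** The text supports neither. Sample size gives a generic two-mean hypothesis and an allocation ratio. The Discussion lists three different controls and does not pool them. How each contrast will be interpreted may be set out in a full protocol or analysis plan that is not shown.

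**The size is assumed.** Correct. Nor are 15% to 46% type I error rates for an overall-effect question, where expectation is partly a genuine component of the difference. They count as false positives only if the result is read as a specific effect of needling.

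**Outcome assessors might also be unblinded by group 4 patients.** That is a separate matter. Quality assurance keeps assessors blinded and out of treatment delivery, and an article may leave an instruction on disclosure to the full protocol.

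**Conclusion.** The statement that all patients are blinded is wrong as written, because the article's own description of group 4 and of its blinding measures contradicts it. This conclusion needs no assumption about bias. Since the primary WOMAC score is self-reported, the individualized versus no-acupuncture contrast is open-label and mixes needling with expectation, attention and reporting bias.

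The extent is one arm in four, one patient in six, and one of the three contrasts with individualized acupuncture. The possible effect on that contrast, about 15% to 46% significant results with no specific effect, rests wholly on the assumed 0.2 to 0.4 SD shift and an unadjusted test, and serves only as illustration.

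The point does not extend to the sample size or to the contrasts among individualized, standard and sham acupuncture, which the design intends to be patient-blind. How well that blinding works in practice is a different question, not judged here.

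**What to change.** 1. In the abstract, Study design, and Randomization and blinding, say that patient blinding applies to groups 1 to 3 only and that group 4 is an open control. Bring the Discussion sentence into line.
2. State that any conclusion on the specific efficacy of individualized acupuncture rests on the individualized versus sham contrast.
3. State that individualized versus no acupuncture is reported as an open-label overall effect that includes expectation, attention and self-reporting.

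The cost is a few sentences. Arms, endpoints, the ANCOVA and the sample size stay as planned. The price is a more modest claim for the untreated contrast.

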### Treatment

Patients will be randomly allocated into four treatment groups: 1. individualized, meridian-based syndrome differentiation and Sa-am acupuncture treatment;2. standard acupuncture treatment;3 sham acupuncture treatment; and 4. no acupuncture treatment. Patients in groups 1 to 3 will be treated twice weekly for 6 weeks. The trial length was based on a survey of certified oriental medicine doctors, in which 50.6% of respondents indicated that treatment for over 5 weeks is necessary to treat chronic knee pain, such as that caused by OA.

For patients with bilateral OA, the side with more pain at baseline, as assessed by a VAS, will be treated and evaluated throughout the study.

#### General acupuncture preparation and needling technique

To ensure that the study is single-blinded and that patients are not aware of the differences between treatments, we propose using a Park sham needle guide-tube [23,24] for all three acupuncture treatment groups. This will ensure that the patient will not observe any outwardly discernible differences among individualized, standard and sham acupuncture, although the penetration of the needles will differ among these three groups.

Prior to needle insertion, the area of the skin will be sterilized. Acupuncture will be performed using sterile stainless steel disposable acupuncture needles (DongBang Acupuncture Inc, Korea).The depth of insertion at each point was predetermined to be within the normal range of 8 mm to 30 mm, depending on the location of the point. Following needle insertion, the acupuncture point will be stimulated using bidirectional rotations of the needle sleeve, to achieve the sensation known as Deqi.

In patients randomized tothe individualized and standard acupuncture groups, an electroacupuncture device (STN-111,StraTek Co, Korea) will be used to provide electrical stimulation to the proximal acupoints, with the clinician adjusting the intensity so that the patientfeels an uncomfortable but not painful sensation. The needles will be kept in place for 20 minutes.

Due to ethical considerations, patients who have previously taken analgesics and non-steroidalanti-inflammatory drugs (NSAIDs) will be allowed to continue to take these medications during the study period. However, we will request that patients avoid physical therapy as much as possible to ensure that our results reflect the role of acupuncture therapy, not other forms of treatment. Patients will be questioned about having received medication at each visit and this information will be recorded for analysis of the data.

